### Intervention training and monitoring

Some providers who conduct standard intake assessments at the participating study sites will be recruited to deliver the MII intervention. We will have separate intake providers deliver the MII and IAU conditions to interested participants. The MII intake providers will participate in a two-day MI training workshop (total of 8 h). The training includes a series of activities focused on increasing trainees’ knowledge and skills in the areas of client engagement (e.g., “A Taste of MI” exercise), therapeutic partnership (e.g., “Personal Values Card Sort” exercise), reflective listening (e.g., “Complexifying Reflections”), and client language (e.g., “Identifying Change Talk”). The workshop is comprised of educational materials and experiential exercises from the Motivational Interviewing Network of Trainers (MINT) Resources for Trainers. Following the workshop, MI intake providers will complete at least three individual feedback and coaching sessions, in accordance with recommended benchmarks of quality MI training [42, 43]. Each session will be scheduled after the intake providers complete a baseline audio-recorded clinical work sample with a standardized or actual patient. The work sample will be rated using the Motivational Interviewing Treatment Integrity (MITI) [44]. The clinical trial will begin after the MII intake providers reach proficiency on the MITI from these work samples. The MII intake providers also will participate in weekly supervision during the trial to assure ongoing adherence and competence to the MII intervention. The training workshop, feedback and coaching sessions, and weekly supervision will be provided by the first and second author, both of whom are licensed clinical psychologists and members of the MINT.

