### Statistical analyses

#### Effectiveness outcomes

The primary effectiveness endpoints for this study will be medical record-verified client entry into treatment (completion of a 1st treatment session after the intake), number of treatment sessions attended, and client completion of treatment (i.e., based on review of treatment attendance and discharge records from assessor blind to intake condition). Analyses will be conducted using intent-to-treat principles [55], with all randomized participants included in the denominator for calculating engagement outcomes. Two binary logistic regression analyses will be used to compare the two intake conditions on the dichotomous outcomes of treatment entry and treatment completion. A negative binomial regression analysis will be used for the count outcome of number of treatment sessions attended. The following covariates will be included in each analysis: participant’s age, gender, race/ethnicity, substance use type, and pre-intake level of motivation. Further, we will explore possible therapist effects on each effectiveness outcome by performing one-way analyses of variance, specifying therapist as a random factor. We will obtain the percent of variance explained by the therapist by dividing the variance for the therapist factor by the total variance.

To evaluate mechanisms of effectiveness, separate mediation analyses will be performed on change in client motivation and therapeutic alliance on the three engagement outcomes. We will conduct logistic regression analyses for the two dichotomous outcomes and a negative binomial regression analysis for the count outcome. To explore whether observed direct effects are mediated by client motivation and therapeutic alliance, a bootstrapping method will be used (Preacher et al. 2008), providing a powerful test of mediation [56].

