There are some limitations of the proposed study. First, clients allocated to the MII condition may be contacted by the study site 24 h after their intake to complete required paperwork for treatment enrollment. Most addiction treatment programs are required to collect certain client information at the outset for external agencies (e.g., funding agencies, health insurance companies). The additional contact to collect the required information may impact client engagement in treatment, though we hope the delay in collecting the information will help mitigate any negative impacts of the information collected and maximize the potential impact of the MII on client engagement outcomes. Second, it may be difficult to train study site intake providers to MI proficiency as evidenced in prior studies, and given their myriad of job duties (e.g., client caseload, administrative tasks, staff meetings) [31]. To address possible challenges with intake providers having the time to be trained in MI and/or to deliver the MI condition, licensed psychologists or advanced clinical psychology graduate students trained in the MI intake intervention will be available to serve as MI intake providers while study site intake providers will serve as intake-as-usual providers. The research team will train all study site personnel in MI either before or after the clinical trial, depending on whether study site intake providers are available serve as MI intake therapists.

This is the first trial to evaluate the effect of a pure MI intake intervention on treatment engagement in clients seeking outpatient addiction treatment programs and thus to provide evidence on how to reduce attrition in addiction treatment. Achieving study aims can demonstrate how aligning the theory and application of MI can improve clients’ entry and engagement in addiction treatment, a point of delivery that currently has the highest rate of attrition. If promising results are achieved, a larger, multisite trial with treatment programs across the United States can lead to external agencies approving the delay of standard intake assessment until clients are engaged and committed to treatment success.

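### Intake providers are nested in arm, but the outcome regressions treat clients as independent, and the separate therapist ANOVA omits arm; type I error exceeds 5% if outcomes vary by provider

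*Protocol article*

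**What the plan says.** Under Intervention training and monitoring, the protocol article states: "We will have separate intake providers deliver the MII and IAU conditions to interested participants". The limitations in the Discussion describe a fallback if site staff lack time to train in or deliver MII. Licensed psychologists or advanced graduate students "will be available to serve as MI intake providers while study site intake providers will serve as intake-as-usual providers". Either way, no provider is described as working in both arms.

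Under Effectiveness outcomes the models are named. For the binary outcomes: "Two binary logistic regression analyses will be used to compare the two intake conditions on the dichotomous outcomes of treatment entry and treatment completion". For the count: "A negative binomial regression analysis will be used for the count outcome of number of treatment sessions attended". The covariates are "participant’s age, gender, race/ethnicity, substance use type, and pre-intake level of motivation". Neither provider nor site is among them, and no random effect or clustered variance is mentioned.

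Therapist then appears in a separate step: "we will explore possible therapist effects on each effectiveness outcome by performing one-way analyses of variance, specifying therapist as a random factor". Its output is descriptive: "We will obtain the percent of variance explained by the therapist by dividing the variance for the therapist factor by the total variance". Nothing says what follows from that percentage.

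**The concern.** When each provider works in only one arm, differences between providers are part of the error of the arm comparison. A model that counts 150 independent clients leaves that component out of the standard error. A few unusually engaging, or unengaging, intake providers in one arm could then look like an effect of MII.

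The article gives reason to expect some provider variation. Its section on the theoretical basis for MII attributes the benefit of MI to how well the therapist uses the therapeutic process, and the Discussion warns that training providers to proficiency may be hard. The comparison at stake is the primary one, treatment entry. The Discussion wants the result to inform wider use of a treat-first approach and a larger multisite trial, so inference has to reach beyond the providers who happen to take part.

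The planned side analysis does not fill the gap. Because therapist is nested in arm and arm is left out, a true arm effect is counted as therapist variance.

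**Working it through.** **The plan's own figure.** The article states no provider count, ICC, alpha or type I error. The nearest figure is power of 0.80 with 75 per arm at d = 0.24, computed with no allowance for clustering. It does not reproduce: Φ(0.24 × √(75/2) − 1.96) = Φ(−0.49) ≈ 0.31 two-sided (0.43 one-sided). That is a separate matter, and nothing below depends on it.

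**Inputs.**
- 75 clients per arm (Sample size and power analysis).
- Entry of 56% under usual intake, taken as 1 − 0.44 from the Background figure for clients who do not return after intake. Its use here is an assumption.
- Two-sided alpha of 0.05: assumed.
- Providers per arm, k = 2 to 10: assumed.
- Provider ICC of 0 to 0.10: assumed.

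**Step 1: type I error of the planned arm test.** With m = 75/k clients per provider, the design effect is DE = 1 + (m − 1) × ICC. The true standard error is √DE times the one the model reports, so the actual error is 2 × [1 − Φ(1.96/√DE)].

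Example: k = 4, ICC 0.02. m = 18.75, DE = 1 + 17.75 × 0.02 = 1.355, √DE = 1.16, 1.96/1.164 = 1.68, error 9.2%.

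| Providers per arm | m | ICC 0 | 0.01 | 0.02 | 0.05 | 0.10 |
|---|---|---|---|---|---|---|
| 2 | 37.5 | 5.0% | 9.3% | 13.6% | 24.4% | 36.3% |
| 4 | 18.75 | 5.0% | 7.1% | 9.2% | 15.4% | 23.9% |
| 8 | 9.375 | 5.0% | 6.0% | 7.0% | 10.0% | 14.8% |
| 10 | 7.5 | 5.0% | 5.8% | 6.5% | 8.9% | 12.7% |

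The correct interval is √DE times as wide as the planned one: 1.03 (k = 10, ICC 0.01), 1.16 (k = 4, ICC 0.02), 1.37 (k = 4, ICC 0.05) and 1.68 (k = 2, ICC 0.05).

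**Step 2: check by simulation.** Beta-binomial provider effects, 56% entry in both arms, unadjusted logistic Wald test, 100,000 runs per setting. For ICC 0.01, 0.02, 0.05 and 0.10 the rejection rates are 9.2%, 13.8%, 24.6% and 37.5% (k = 2); 7.0%, 9.3%, 15.4% and 24.4% (k = 4); 6.0%, 7.0%, 10.0% and 14.9% (k = 8). At ICC 0 the rate is about 5.0%. This agrees with the formula.

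**Step 3: what the one-way ANOVA reports when therapists do not differ.** Let K = 2k therapists and δ = the arm difference in entry. Half the therapist means lie δ/2 above the overall mean and half δ/2 below, so the apparent therapist variance is K(δ/2)²/(K − 1). The within-therapist variance is the average of p(1 − p) over the arms.

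For 56% versus 71% and k = 2: 4 × 0.075²/3 = 0.0075; within = (0.2464 + 0.2059)/2 = 0.2262; share = 0.0075/0.2337 = 3.2%. With k = 8 it is 2.6%. For 56% versus 66% the share is 1.1% to 1.4%, and for 56% versus 76% it is 4.7% to 5.9%. A reported 3% could therefore be all arm effect or all therapist effect.

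**Step 4: what a proper interval costs.** On the risk-difference scale at 56% entry the planned half-width is 1.96 × √(2 × 0.56 × 0.44/75) = 1.96 × 0.081 = 16 percentage points. With ICC 0.05 and a t-quantile on (total providers − 2) degrees of freedom:
- k = 2: 4.303 × 0.081 × 1.68 ≈ 59 points
- k = 3: 2.776 × 0.081 × 1.48 ≈ 33 points
- k = 4: 2.447 × 0.081 × 1.37 ≈ 27 points

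**The case against.** The strongest reply is that the size of the problem is unknown. Provider numbers and the ICC are not stated, and with 8 to 10 providers per arm and ICC 0.01 the error is only about 6%. The article also describes steps that limit variation within arm: MII providers must reach proficiency on a fidelity rating before the trial starts, with at least three coaching sessions and weekly supervision during it, and usual intake follows a semi-structured guide. This stands. It bears on which ICC is plausible, but it does not make the ICC zero.

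A second reply is that an analysis plan not shown may add a provider term. But the article is not silent here: it names the models, lists their covariates and sets out a different treatment of therapist.

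A reader might also infer more than the text supports:
- That type I error is well above 5% outright. That needs few providers or a larger ICC. Two sites make few providers plausible, but this is an inference.
- That the ANOVA cannot detect therapist effects. It can. Omitting arm inflates the therapist share rather than hiding it. The fault is that it mixes the two sources and changes nothing in the arm comparison.
- That an ANOVA on binary or count data is invalid in itself. The variance ratio is a recognised ICC estimator for binary data, and its point estimate does not need normality.
- That arm and provider type are fully aliased. This holds only if the fallback is used throughout. The main text plans for site providers to deliver MII, and the fallback is disclosed as a limitation.

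**Conclusion.** The point holds in conditional form. Provider is nested in arm, the stated regressions treat clients as independent, and the therapist ANOVA neither separates therapist from arm nor feeds into the arm inference. If outcomes vary by provider, the planned intervals are too narrow and type I error exceeds 5%: about 6% (8 to 10 per arm, ICC 0.01), 9% (4 per arm, ICC 0.02), 15% (4 per arm, ICC 0.05) or 24% (2 per arm, ICC 0.05), and 5% at ICC 0.

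These figures rest on assumed provider numbers and ICCs, equal caseloads, a two-sided 5% test, and inference to providers beyond those in the trial. They are worked for a binary outcome without covariates. The direction also applies to completion and session counts, though their ICCs may differ. Of the documents' own facts, the nesting and the model specification are certain; the size is not.

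**What to change.** In the logistic and negative binomial models, add a random intercept for intake provider (nested in arm), keep arm and site as fixed effects, and base the arm interval and test on small-sample degrees of freedom. That is about the number of providers minus 2, less one more for site if each provider works at a single site. Report the therapist variance or ICC from that model in place of the one-way ANOVA, together with the number of providers per arm.

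If outside clinicians deliver MII under the fallback, state that the contrast is MII by external clinicians versus usual intake by site staff. Restricting the analysis to intakes by site-employed providers is not a remedy. It selects clients after randomisation by who saw them, no random assignment to providers is described, and it departs from the stated intent-to-treat principle.

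The change itself is analysis wording. The price is a wider interval for the arm effect. With only 2 or 3 providers per arm it may be too wide to be informative, and no analysis can then fully separate provider from arm; the plan should say so.

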#### Implementation outcomes

Descriptive statistics, chi-square tests, and between-group analyses of quantitative measures will be performed. We will use a combined deductive and inductive thematic analysis approach [57] to qualitative data. Four raters will analyze qualitative data from interviews using NVivo software and in accordance with the six steps outlined by Braun and Clarke [57], and at least 50% of interviews will be double-rated to calculate inter-rater reliability. We will use deductive analysis to identify facilitators and barriers of MII implementation across the five CFIR domains. An inductive approach will then be used to generate themes and sub-themes from the qualitative data. Several analyses combining quantitative and qualitative data will be performed to fully conceptualize personnel perspectives on the intake process, to identify the most salient factors to implementation, and to determine which factors are common and unique across sites. Implementation data also will provide direction for a future implementation trial.

### Data safety management

Data collection procedures will be monitored by a Data Safety and Monitoring Board (DSMB) consisting of six clinical and experimental researchers independent from the sponsor and with no competing interests. DSMB members will receive bi-annual progress reports to determine whether to continue recruitment, propose a protocol amendment, or stop recruitment for the trial. Any adverse events will be reported to the principal investigator who will report it to the DSMB and NIDA in an annual progress report. The DSMB members will provide a recommendation on whether and how to proceed with the study. Serious adverse events and unanticipated problems will be reported within 24 h of occurrence to the institution’s IRB and to the study’s NIDA Program Officer in addition to the submission of a complete report.

## Discussion

The purpose of this trial is to determine the effectiveness of an MII intervention on client engagement and retention in outpatient addiction treatment. The MII trial also seeks to understand the potential for future sustainable implementation of MII across outpatient addiction treatment programs. As the field of addiction treatment has shifted focus to a recovery-oriented model of care, a wealth of person-centered treatment services focused on the whole person have been developed. In fact, extant research has revealed that services that better attend to client goals and values and also focus on non-substance related outcomes (e.g., well-being) predict client initial success and are better maintained over time [8].

The state of New Mexico implemented a Treat First model on January 11, 2016, which permits certified behavioral health facilities to delay the comprehensive intake assessment until the fourth session, allotting time for providers to develop rapport with clients and to facilitate client motivation to enter and remain in treatment. The Treat First model was developed with agreement by Medicaid and state-funded non-Medicaid funds to cover the cost of services without agencies needing to alter their billing process or being found noncompliant for not conducting the intake assessment and treatment plan during the first visit. The only requirement is that facilities become certified as a Treat First Agency (https://treatfirst.org/talks/how-to-become-a-treat-first-agency/). To date, 32 behavioral health agencies have been certified to use the Treat First Model, most of which are child or adult mental health treatment agencies. An evaluation of the Treat First model in its first year found that approximately 66% of clients came to all scheduled appointments. Although promising, no empirical investigations, to our knowledge, have looked at the utility of an evidence-based intervention during the first contact or its impact on organizations. By working with two addiction treatment programs that *do not* currently adhere to the Treat First Model, the current trial offers a comparative investigation of the utility of the standard comprehensive assessment versus an evidence-based intervention during intake, and thus can guide the dissemination of the Treat First Model to other treatment programs. Further, by simultaneously evaluating the feasibility of implementing an evidence-based intervention at intake, programs can identify ways to modify their intake procedures to engage clients while also adhering to state and federal agency requirements.

There are some limitations of the proposed study. First, clients allocated to the MII condition may be contacted by the study site 24 h after their intake to complete required paperwork for treatment enrollment. Most addiction treatment programs are required to collect certain client information at the outset for external agencies (e.g., funding agencies, health insurance companies). The additional contact to collect the required information may impact client engagement in treatment, though we hope the delay in collecting the information will help mitigate any negative impacts of the information collected and maximize the potential impact of the MII on client engagement outcomes. Second, it may be difficult to train study site intake providers to MI proficiency as evidenced in prior studies, and given their myriad of job duties (e.g., client caseload, administrative tasks, staff meetings) [31]. To address possible challenges with intake providers having the time to be trained in MI and/or to deliver the MI condition, licensed psychologists or advanced clinical psychology graduate students trained in the MI intake intervention will be available to serve as MI intake providers while study site intake providers will serve as intake-as-usual providers. The research team will train all study site personnel in MI either before or after the clinical trial, depending on whether study site intake providers are available serve as MI intake therapists.

This is the first trial to evaluate the effect of a pure MI intake intervention on treatment engagement in clients seeking outpatient addiction treatment programs and thus to provide evidence on how to reduce attrition in addiction treatment. Achieving study aims can demonstrate how aligning the theory and application of MI can improve clients’ entry and engagement in addiction treatment, a point of delivery that currently has the highest rate of attrition. If promising results are achieved, a larger, multisite trial with treatment programs across the United States can lead to external agencies approving the delay of standard intake assessment until clients are engaged and committed to treatment success.

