Addiction treatment personnel also will be included as participants to evaluate implementation feasibility. Personnel participants will comprise two groups: study-involved and study-naïve personnel. Study-involved personnel will be eligible to participate if they are English-speaking adults currently employed at one of the two study sites. Study-naive personnel will be eligible to participate if they are English-speaking adults who are currently employed at an addiction treatment program in the state of New Mexico. Study-involved personnel will be recruited from the two study sites but excluded from participation if they currently hold a leadership position (i.e., owner or clinical director). Study-naïve personnel will be recruited via email from treatment agency directors across the state of New Mexico and excluded if their job responsibilities include providing medical or administrative services. No manipulation or randomization procedures are in place for personnel participants. Whereas study-involved personnel participants will be asked to complete all implementation procedures, including pre-MII training assessments, optional MII training, and post-trial assessments and interview, the study-naïve personnel will be asked to complete only post-trial implementation procedures (i.e., post-trial assessments and interview).

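### The plan allows staff who deliver intake-as-usual to be trained in MI before or during the trial, which undercuts the separate-provider safeguard and may dilute the contrast

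*Protocol article*

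**What the plan says.** Three places in the protocol article bear on who is trained in MI and when.

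- **Methods, Intervention training and monitoring.** MII providers come from the sites' own intake staff: "Some providers who conduct standard intake assessments at the participating study sites will be recruited to deliver the MII intervention". The arms are kept apart by personnel: "We will have separate intake providers deliver the MII and IAU conditions to interested participants". The workshop, the coaching sessions and the proficiency requirement are described for MII providers only, as is supervision: "The MII intake providers also will participate in weekly supervision during the trial to assure ongoing adherence and competence to the MII intervention".
- **Methods, Study participants.** The definition of study-involved staff is wide: "Study-involved personnel will be eligible to participate if they are English-speaking adults currently employed at one of the two study sites". Owners and clinical directors are excluded; intake providers are not. What these staff are to do is listed as "including pre-MII training assessments, optional MII training, and post-trial assessments and interview".
- **Discussion, limitations paragraph.** If site providers lack the time, psychologists or graduate students will deliver MII and site providers will deliver IAU. On training, the paragraph states: "The research team will train all study site personnel in MI either before or after the clinical trial". The same sentence makes the choice between the two times conditional: "depending on whether study site intake providers are available serve as MI intake therapists".

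**The concern.** Using different providers in each arm limits contamination only if those delivering IAU have not been taught the experimental method. The Discussion sentence and the optional training both leave room for them to be taught it before or while clients are being randomised.

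The trial is meant to test replacing the comprehensive assessment with MI, and the Background contrasts this with earlier studies that mixed MI with assessment. An MI-trained provider giving the IAU interview could recreate that mixture in the comparator. Any resulting bias would be towards no difference on treatment entry, the primary outcome in the Outcomes section. It could also reach motivation and alliance, the two proposed mechanisms, because these are what MI skills target. Contamination of this kind is hard to undo once it has happened, whereas preventing it is a matter of scheduling.

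**Working it through.** **Step 1: the sections side by side.**

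| Question | Intervention training and monitoring | Study participants | Discussion |
|---|---|---|---|
| Who is trained? | MII providers | Study-involved personnel, optionally | All staff at the sites |
| When? | Before the trial starts, with supervision during it | No date; listed between the pre-training and post-trial assessments | Before or after, depending on availability of site intake staff |
| Are IAU providers excluded? | By implication | No | No |

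The Discussion sentence has two branches. If site staff deliver MII, training precedes the trial; if outside therapists deliver it, training follows. The Methods make the first branch the main plan, and that is the branch in which IAU providers can be trained early.

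**Step 2: the plan's own power figure.** Sample size and power analysis states power 0.80 at d = 0.24 with 75 per condition. Alpha and sidedness are not stated; two-sided 0.05 is assumed, with SD = 1.

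- Standard error = √(2/75) = 0.1633.
- Power = Φ(0.24/0.1633 − 1.960) = Φ(−0.490) = 0.31 (0.43 if one-sided).

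The stated figure does not reproduce. That is a separate issue, and this point does not depend on it. It matters here only because the design has no spare power to absorb dilution.

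**Step 3: illustration of dilution.** Assumed inputs:

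- IAU entry rate 56%, from the Background statement that 44% do not return after intake (1 − 0.44). This is not a stated design input.
- MII entry rate 77.4%, chosen because it gives power 0.80 with 75 per arm.
- Leakage f, the share of the effect that passes into IAU. It is purely assumed.

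Diluted IAU rate: p_c = 0.56 + f × (0.774 − 0.56). With p̄ the mean of p_c and 0.774:

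- se0 = √(2p̄(1 − p̄)/75)
- se1 = √([p_c(1 − p_c) + 0.774 × 0.226]/75)
- Power = Φ([0.774 − p_c − 1.960 × se0]/se1)

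| f | p_c | Difference | se0 | se1 | Power |
|---|---|---|---|---|---|
| 0 | 0.560 | 0.214 | 0.0770 | 0.0750 | 0.80 |
| 0.05 | 0.571 | 0.203 | 0.0766 | 0.0748 | 0.76 |
| 0.10 | 0.581 | 0.193 | 0.0763 | 0.0747 | 0.72 |
| 0.25 | 0.614 | 0.161 | 0.0753 | 0.0741 | 0.57 |

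**Step 4: cross-check on the d scale**, taking the diluted effect as d(1 − f). At d = 0.46, about the smallest effect that 75 per arm detects with 80% power, f = 0.25 gives 0.345 and power falls from 0.80 to 0.56. At d = 0.24, f = 0.25 gives 0.18 and power falls from 0.31 to 0.20.

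**The case against.** The strongest reply is that the Discussion sentence can be read distributively: everyone is eventually trained, MII providers before the trial and the rest after it. That fits the Methods, which confine the workshop and coaching to MII providers. The sentence also stands in a limitations paragraph, the optional training carries no date, and the timeline figure is not visible here. This stands as a possible reading, but the text does not fix it, and the clause that sets the timing applies to all site personnel together.

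Second, even a trained IAU provider still conducts a 60-to-90-minute semi-structured assessment, and a workshop is not proficiency. The article itself reports that mixing MI with assessment has often had no effect on engagement. On that view leakage may be small. This stands as a reason not to claim any particular amount; it does not rule leakage out.

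Several stronger readings are tempting but unsupported.

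- **MII providers as more motivated volunteers, biasing the other way.** The text says only that some providers will be recruited, not how they are chosen.
- **Spill-over through clinicians who treat clients later.** Clients either attend the first scheduled session or do not before any such clinician can treat them, so this cannot explain treatment entry. For later attendance the exposure would be common to both arms.
- **No monitoring of IAU sessions for MI content.** None is described, but a condensed article may leave control-arm monitoring to the full protocol.

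**Conclusion.** The point holds as a conflict over who is trained and when. On the natural reading, the main plan permits IAU providers to be MI-trained before the trial, and the optional training does not exclude them. This weakens the one stated means of keeping the arms apart, and the contrast may be diluted towards no difference.

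The exposure is conditional. If outside therapists deliver MII, the Discussion route closes, though the undated optional training would still need a stated time. A reader might infer that dilution is certain or large; the documents support neither. The fall in power from 0.80 to 0.72 or 0.57 rests on an assumed 56% versus 77.4% effect and assumed leakage of 10% or 25%. At 5% leakage it would be 0.76. The point should be settled before enrolment, but it does not show that the trial's result would be invalid.

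**What to change.** Reconcile Study participants, Intervention training and monitoring, and the Discussion with one rule: only assigned MII providers are trained in MI before or during enrolment. Staff delivering IAU receive any MI training, the optional training included, only after the last randomised client's intake at their site.

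The Discussion already allows training after the trial, so this changes timing and needs no extra staff or participants. There are two costs. Some staff wait for training they have been promised. And because the personnel survey follows immediately after the trial, it will capture training exposure mainly among MII providers, which the implementation analysis should acknowledge.
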